### 2.8. Baseline Characteristics and Treatment

The baseline characteristics of enrolled patients will be prospectively collected, including baseline factors such as age, height, weight, handedness, employment status, existing comorbidities, pre-admission mRS, and frailty; disease factors such as culprit vessel, lesion, and national institutes of health stroke scale [31]; biochemical data such as C-reactive protein, lymphocyte count, and serum albumin; and nutrition factors such as the Malnutrition Universal Screening Tool [32] at admission. The National Institutes of Health Stroke Scale will be recorded at admission, day 7, and at discharge. Details of treatments that may affect outcomes, such as surgery, use of Tissue Plasminogen Activator, noninvasive ventilation, mechanical ventilation, and tracheostomy, will also be prospectively collected.

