### 2.13. Rehabilitation Dose

Rehabilitation dose is defined using the MQS over days 1–7 post-admission. MQS combines mobilization level (assessed using the ICU mobility scale [33]) and duration (measured with a stopwatch). Only active mobilization time is included; preparation or rest is excluded. The MQS is averaged across the first 7 days to reflect the daily rehabilitation dose (Japanese version MQS [21]. It should be noted that rehabilitation itself continues beyond the first 7 days until hospital discharge, according to each institution’s standard practice. After discharge, patients typically continue rehabilitation in post-acute care facilities or outpatient/community settings, depending on their medical condition and regional healthcare resources. Functional outcomes at 90 days will therefore reflect the combined effect of early inpatient rehabilitation and subsequent standard care.

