### 2.14. Statistical Methods

There is no maximum sample size for this study; however, the outcome may be subject to targets or maximum sample sizes, which will be specified in the relevant sub-protocol. The expected sample size is ≥200 patients (minimum 10 patients/facilities, ≥20 facilities) to provide a sufficient number of different rehabilitation doses to predict functional outcomes and build robust models for protocol use. To avoid over-representation of some centers, data collection is limited to 50 patients per facility. Patient enrollment will therefore not be strictly equal across hospitals; each facility is expected to enroll at least 10 patients, with a maximum of 50 patients, depending on their clinical volume. This strategy ensures diversity in practice patterns while preventing over-representation of any single center. The number of enrolled patients and facilities is a sufficient sample size to capture the various variations in practice and treatment. It is considered feasible to collect a sample of this calculated size because each participating facility should be able to enroll at least one patient per month based on the number of stroke patients hospitalized at each facility in the past.

Baseline characteristics and outcomes will be summarized using descriptive statistics. Continuous variables will be presented as means with standard deviations (SDs) or medians with interquartile ranges (IQRs), while categorical variables will be presented as frequencies and percentages (*n*, %).

The primary analysis will examine the association between the mean rehabilitation dose (MQS score) during the first 7 days of hospitalization and the primary outcome of a favorable functional outcome (mRS ≤ 2) at 90 days. This association will be evaluated using a multivariable logistic regression model. The model will be adjusted for a pre-specified set of covariates selected for their established prognostic significance, including age, sex, pre-admission mRS, baseline National Institutes of Health Stroke Scale (NIHSS) score, stroke subtype (ischemic or hemorrhagic), and participating facility (as a random effect).

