For secondary outcomes, multivariable linear regression models will be used for continuous variables, such as the Barthel Index. A pre-specified subgroup analysis will be conducted to explore whether the effect of rehabilitation dose is modified by initial stroke severity. An interaction term between the MQS score and the severity category (defined by baseline NIHSS) will be introduced into the primary model.

Time-to-event outcomes will be analyzed using Kaplan–Meier curves and Cox proportional hazards regression models, adjusted for baseline characteristics. For survival analysis, patients will be stratified into groups based on quartiles of rehabilitation volume and pre-defined stroke severity categories. Missing data for covariates will be handled using multiple imputation under the missing-at-random assumption. The primary analysis will be based on the pooled results from the imputed datasets, with a complete-case analysis performed as a sensitivity analysis.

All statistical analyses will be performed using JMP (version 13.0; SAS Institute, Cary, NC, USA) and IBM SPSS software (version 23.0; IBM, Armonk, NY, USA). A two-sided *p*-value of <0.05 will be considered statistically significant.

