## 3. Discussion

This multicenter prospective cohort study aims to evaluate the association between rehabilitation dose quantified using MQS and functional outcomes in patients with acute stroke. The study is designed to address the current lack of evidence regarding optimal early mobilization parameters, particularly in the acute phase of stroke care. While early rehabilitation has been widely promoted in recent years, clinical practices remain variable, with no established consensus on ideal dose, timing, or intensity [34]. Our study is the first large-scale investigation in Japan to quantitatively assess daily rehabilitation dose using a validated measure and its relationship with long-term independence in activities of daily living.

Prior studies on early mobilization in stroke patients have yielded inconsistent findings. For instance, while very early mobilization was associated with poorer outcomes in some randomized controlled trials [14], further post hoc analyses have suggested that mobilization delivered in shorter, more frequent sessions may improve recovery [15]. These conflicting findings may be attributed to differences in rehabilitation intensity, timing, patient severity, and methodological inconsistencies across studies [12]. By incorporating MQS, which integrates both mobilization level and duration, our study provides a more comprehensive and standardized approach to measuring rehabilitation exposure [16]. Furthermore, by stratifying patients based on stroke severity, our study will allow exploration of differential responses to rehabilitation dose, which may help define individualized, severity-specific strategies.

Another strength of this study is the integration of multiple functional, physical, and clinical outcomes, including mRS, Barthel Index, Medical Research Council score, muscle ultrasound, and frailty assessments, which enables a multifaceted evaluation of recovery. The inclusion of ultrasound to objectively assess atrophy of the rectus femoris provides novel insight into the impact of early mobilization on muscle preservation, which has been relatively underexplored in stroke rehabilitation research [35,36]. Additionally, our protocol controls for key patient-level and institutional factors, including comorbidities, nutritional status, rehabilitation policy, and institutional staffing, enhancing the robustness of our multivariate analyses.

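### The Discussion says comorbidities, nutrition, rehabilitation policy and staffing are controlled, but the pre-specified primary model names none of them, and its facility random effect covers only the last two, in part

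*Protocol article*

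**What the plan says.** The protocol article describes adjustment in two places.

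- Section 2.14 (Statistical Methods), primary analysis: "The model will be adjusted for a pre-specified set of covariates selected for their established prognostic significance", followed by the list "including age, sex, pre-admission mRS, baseline National Institutes of Health Stroke Scale (NIHSS) score, stroke subtype (ischemic or hemorrhagic), and participating facility". Facility enters as "participating facility (as a random effect").
- Section 3 (Discussion): "our protocol controls for key patient-level and institutional factors, including comorbidities, nutritional status, rehabilitation policy, and institutional staffing". The sentence goes on to credit this with making the multivariable analyses more robust.

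Three other sections bear on the point.

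- Section 2.8 collects comorbidities, frailty and the Malnutrition Universal Screening Tool at baseline. It also collects "Details of treatments that may affect outcomes, such as surgery, use of Tissue Plasminogen Activator", along with ventilation and tracheostomy.
- Section 2.3 records institutional characteristics before enrollment and keeps them fixed during the study.
- Section 2.13 defines the exposure: "MQS combines mobilization level (assessed using the ICU mobility scale [33]) and duration", averaged over the first seven days.

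For secondary outcomes section 2.14 says: "For secondary outcomes, multivariable linear regression models will be used for continuous variables, such as the Barthel Index". It lists no covariates for these models.

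**The concern.** The two descriptions of adjustment do not agree. A report that follows section 2.14 and repeats the Discussion would credit the analysis with adjustments that were not made.

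The choice of covariates matters more here than in many cohorts because of how the exposure is built. A patient who can stand or walk in the first week can score a higher mobilization level than one who can only be moved passively. MQS is therefore likely to carry some information about prognosis as well as about the care delivered. Section 2.14 chose its covariates for prognostic value, and does not say that they were also chosen as determinants of dose. If fitter patients receive more dose and also recover better, an association can appear where dose has no effect. The Discussion expects the results to inform severity-specific dose targets, so readers will rely on the claimed control.

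**Working it through.** **1. The two lists side by side**

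| Factor the Discussion says is controlled | Collected? | Named in the section 2.14 model? | Covered indirectly? |
|---|---|---|---|
| Comorbidities | Yes, 2.8 | No | No |
| Nutritional status | Yes, 2.8 | No | No |
| Rehabilitation policy | Documented per facility, 2.3 | No | Partly, by the facility random effect |
| Institutional staffing | Documented per facility, 2.3 | No | Partly, by the facility random effect |

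Named terms: 0 of 4. The coverage of the two institutional factors is partial because a random intercept is taken to be independent of MQS. If facilities that deliver more dose also differ in other ways that affect outcome, the intercept does not remove all of that difference.

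**2. Can the size of the confounding be computed?**

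No. The documents give no correlation between patient capacity and MQS, no effect of capacity on outcome and no favorable-outcome rate. The following is an illustration on assumed inputs.

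Set-up: N=200, 1,000 runs per row, true MQS odds ratio 1.0. NIHSS has a log-odds ratio of −1.0 per SD on outcome and a loading of −0.5 on MQS. A capacity factor independent of NIHSS is left out of the model.

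| Loading of omitted capacity on MQS | Log-OR of capacity on outcome | Apparent OR per SD of MQS | Rejection at two-sided 0.05 |
|---|---|---|---|
| 0 | 0.3 / 0.7 | 1.01 / 1.00 | 4% / 5% |
| 0.2 | 0.3 / 0.7 | 1.08 / 1.19 | 8% / 15% |
| 0.4 | 0.3 / 0.7 | 1.18 / 1.44 | 16% / 50% |
| 0.6 | 0.3 / 0.7 | 1.28 / 1.72 | 25% / 84% |

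The result runs from no bias to a large one, according to the assumption.

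The direction is also conditional. With all variables standardized and NIHSS reversed so that high is good, the covariance of capacity and MQS that remains after adjusting for NIHSS is

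r(capacity, MQS) − r(capacity, NIHSS) × r(NIHSS, MQS).

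Take capacity as the only driver of outcome, at 1.5 log-odds per SD:

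- Correlations 0.6, 0.6 and 0.4: 0.6 − 0.6 × 0.4 = 0.36, and the simulated OR is 1.70.
- Correlations 0.4, 0.8 and 0.5: 0.4 − 0.8 × 0.5 = 0, and the OR is about 1.0.
- Correlations 0.4, 0.8 and 0.6: 0.4 − 0.8 × 0.6 = −0.08, and the OR is about 0.84.

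Bias away from the null in favor of dose is thus the natural risk when fitter patients of equal NIHSS receive more dose, but it is not a derived result.

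**3. What the added terms cost**

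The expected sample size is at least 200 (10 patients × 20 facilities, section 2.14). The favorable-outcome rate is assumed to be 40–60%, so the smaller outcome class holds 80–100 patients. The fixed-effect parameters now are MQS, age, sex, pre-admission mRS, NIHSS and subtype, six in all, each coded as one term.

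- As planned: 80/6 = 13.3 to 100/6 = 16.7 events per parameter.
- Three added: 80/9 = 8.9 to 100/9 = 11.1.
- Six added: 80/12 = 6.7 to 100/12 = 8.3.

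At 120 patients (the 10-patient minimum at the twelve hospitals of sections 2.1 and 2.3) the smaller class holds 48–60. The figures are then 8–10 as planned, 5.3–6.7 with three added and 4–5 with six added.

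**The case against.** The case for leaving the model alone has real content.

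- **Confounding is not ignored.** Age, pre-admission mRS, NIHSS and subtype are adjusted for, and patients with pre-hospitalization mRS of 3 or more are excluded. The aim is worded as an association, and the Discussion concedes that causality cannot be established. This stands: the MQS odds ratio is at risk of confounding, and the documents do not show that it is confounded.
- **Institutional factors are not simply missing.** They are constant within a facility, so the facility random effect takes up part of them. This stands. A staffing term estimated from twelve facilities would be imprecise, and separating within- from between-facility dose is a refinement.
- **The list may be open-ended, since it begins with a word that allows more.** This is weak. The list follows a statement that the set is pre-specified. If further covariates were intended, the set has not been fixed.
- **Baseline covariates are not capacity in days 1–7.** This stands. They can reduce that confounding but not remove it.

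Two stronger readings are tempting. A reader might infer that the Discussion also claims control of frailty and treatment. It does not: frailty appears there only among the outcomes ("Medical Research Council score, muscle ultrasound, and frailty assessments, which enables a multifaceted evaluation of recovery"), and treatment is not mentioned as a controlled factor. Their absence from the model is a separate and weaker point. A reader might also infer that the secondary models drop the facility term. One summary sentence that lists no covariates at all does not establish that, and a condensed article may leave the detail to the analysis plan.

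**Conclusion.** The contradiction holds on the text alone. Four factors are said to be controlled and none is a named model term. Comorbidity and nutritional status are not covered at all; policy and staffing are covered in part by the facility random effect.

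The consequence is a risk of residual confounding of the MQS odds ratio, most plausibly away from the null. Its size cannot be computed from the documents. The illustrative odds ratios of 1.08–1.72 under a true null need the assumed loadings of 0.2–0.6 and log-odds ratios of 0.3–0.7, and other equally unsupported correlations give no bias or bias the other way. These figures show why the adjustment set matters and should not be read as estimates for this study.

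**What to change.** 1. **Primary model (section 2.14).** Add covariates already collected at baseline: comorbidity as one summary term, the Malnutrition Universal Screening Tool and the baseline Clinical Frailty Scale. Acute treatment given before the first mobilization may be added; later treatment should not be, because it can follow from the course of days 1–7.
2. **Secondary models (section 2.14).** State that the same covariates and the facility term are used.
3. **Discussion.** Claim control only for factors that are in the model, and describe rehabilitation policy and staffing as partly absorbed by the facility random effect. Say that confounding by capacity during days 1–7 is reduced but not removed.
4. **Optional sensitivity analysis.** Split MQS into the facility mean and the patient's deviation from it, and report both odds ratios.

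The cost is wording and a few degrees of freedom; no new data are needed, and enrollment is not due to begin until June 2026. At n=200, under the assumed 40–60% favorable rate, three added terms leave about 9–11 events per parameter and six leave about 7–8. Keep the added terms few or apply mild shrinkage, more so if enrollment ends nearer 120. If the authors prefer not to extend the model, item 3 alone removes the contradiction but leaves the confounding risk as it is.

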### 2.3. Study Setting

Twelve regional acute care hospitals in the Chubu region will participate (Supplementary materials Figure S1). Institutional characteristics (including the presence of unique clinical protocols, nurse-to-patient ratios, and availability of neurologists or other specialists) will be documented prior to enrollment and remain fixed throughout the study period. Rehabilitation practices vary among institutions but are based on standard references, including the Stroke Treatment Guidelines [20], Japanese Guidelines for Rehabilitation of Critically Ill Patients [23], and the Japanese Guidelines for Nutrition in Critically Ill Patients [24].

All hospitalized stroke patients will be screened within 24 h of admission by the research staff or departmental rehabilitation teams on working days. Eligible patients (if awake and cooperative) or their family members will be approached for consent within the first 24 h of admission, after which data collection will begin (Table 1).

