### 2.11. Rehabilitation Protocol

Participants in the BRIDGE cohort will receive their usual rehabilitation at their respective institutions. We aim to exercise all participants equally every day, based on a five-stage protocol (Level 1: passive range of motion and respiratory physiotherapy, Level 2: active range of motion, Level 3: sitting exercise, Level 4: standing exercise, Level 5: walking exercise) tailored to each participating hospital. In addition, adverse events during implementation will also be indicated with appropriate values in the categories of medical, cardiovascular, respiratory, and neurological problems. In case of deviation from these values, the patient will be immediately placed on bed rest, and the event will be considered an adverse event. After level 5 is achieved, a physiotherapist or occupational therapist will provide each patient with rehabilitation, including muscle strengthening, balance, walking, and stair climbing, for at least 20 min on weekdays, according to the rehabilitation policy of each hospital.

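### The primary model enters MQS once beside a facility random effect, so if hospital dose and hospital outcome are correlated its single odds ratio blends within- and between-hospital associations; a pre-specified companion split would show this

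*Protocol article*

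**What the plan says.** Section 2.14 (Statistical Methods) defines the primary analysis as "the association between the mean rehabilitation dose (MQS score) during the first 7 days of hospitalization and the primary outcome" of mRS ≤ 2 at 90 days. On the model it says "This association will be evaluated using a multivariable logistic regression model". The named adjustments are age, sex, pre-admission mRS, baseline NIHSS, "stroke subtype (ischemic or hemorrhagic), and participating facility (as a random effect"). The list is introduced as non-exhaustive. MQS is the only dose term; no facility-mean MQS, centring or institutional covariate is named. The same model carries the MQS-by-severity interaction. The test level is fixed: "A two-sided *p*-value of <0.05 will be considered statistically significant".

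Four other places bear on how dose and hospital relate:

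- Section 2.3: "Rehabilitation practices vary among institutions but are based on standard references". Local clinical protocols, nurse staffing and specialist availability are recorded before enrolment.
- Section 2.11: "Participants in the BRIDGE cohort will receive their usual rehabilitation at their respective institutions".
- Section 2.13: "MQS combines mobilization level (assessed using the ICU mobility scale [33]) and duration (measured with a stopwatch"). Rehabilitation after day 7 follows each institution's practice, and the 90-day outcome is said to reflect early and later care together.
- Section 2.14, on the enrolment limits per facility: "This strategy ensures diversity in practice patterns while preventing over-representation of any single center".

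The Discussion (section 3) says that rehabilitation policy and institutional staffing are controlled. Neither appears among the covariates in section 2.14.

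**The concern.** Patients differ in MQS for two reasons. Within a hospital, some can do more than others. Between hospitals, some mobilize more as a matter of practice. A random intercept treats what is left of the hospital's effect on outcome as unrelated to MQS. If hospitals with a higher average dose also differ in other care that affects mRS at 90 days, part of that difference passes into the MQS coefficient.

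The coefficient is then a weighted mix of the two associations. The weights depend on cluster size and on how dose varies, and a reader given one odds ratio cannot see the mix. This matters for the uses set out in the Discussion. Dose targets for individual patients need the within-hospital association, whereas facility benchmarking concerns the between-hospital one. One number cannot serve both if they differ.

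**Working it through.** **Stated figure.** Section 2.14 gives 10 patients × 20 facilities = 200, which reproduces. The article gives no power, effect size or event rate, so there is no power calculation to check. Section 2.1 names twelve hospitals, so three layouts were used:

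- 12 × 18 = 216 (twelve hospitals, one patient a month, 18 months);
- 20 × 10 = 200 (the stated minimum);
- 12 × 50 = 600 (the cap).

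**Assumed inputs, not in the documents.** Dose ICC 0.1–0.4; facility SD 0.3–0.5 on the logit scale; correlation ρ between facility dose and facility effect 0, 0.7 or 1; NIHSS log-odds ratio −1 per SD; about 50% favourable outcomes; dose lower with higher NIHSS (coefficient −0.4 against a residual SD of 1). The true patient-level effect of MQS is zero.

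**Simulation.** 600 datasets per setting, random-intercept logistic regression by 15-point Gauss–Hermite maximum likelihood, Wald test at two-sided 0.05. Both models adjust for NIHSS: (a) one MQS term; (b) facility-mean MQS plus deviation from it. The Monte Carlo standard error at 5% is √(0.05 × 0.95/600) = 0.9 points. Odds ratios are per SD of MQS.

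| Setting | Layout | Single term: OR, rejection | Within OR, rejection | Between OR |
|---|---|---|---|---|
| ρ 0, ICC 0.2, SD 0.5 | 12×18 | 0.99, 5.8% | 0.99, 4.7% | 0.95 |
| | 20×10 | 1.00, 4.8% | 1.00, 5.3% | 0.99 |
| | 12×50 | 1.01, 5.5% | 1.01, 4.7% | 0.98 |
| ρ 0.7, ICC 0.1, SD 0.5 | 12×18 | 1.08, 8.2% | 1.00, 5.8% | 2.16 |
| | 20×10 | 1.10, 8.8% | 1.02, 6.2% | 1.84 |
| | 12×50 | 1.04, 8.0% | 1.00, 4.3% | 2.65 |
| ρ 0.7, ICC 0.2, SD 0.3 | 12×18 | 1.08, 8.5% | 1.00, 5.8% | 1.48 |
| | 20×10 | 1.08, 6.7% | 1.00, 4.3% | 1.40 |
| | 12×50 | 1.06, 8.8% | 1.00, 4.0% | 1.56 |
| ρ 0.7, ICC 0.2, SD 0.5 | 12×18 | 1.11, 11.2% | 1.00, 6.2% | 1.99 |
| | 20×10 | 1.14, 12.7% | 1.01, 5.3% | 1.78 |
| | 12×50 | 1.06, 10.7% | 1.00, 5.0% | 2.06 |
| ρ 0.7, ICC 0.4, SD 0.5 | 12×18 | 1.18, 19.5% | 1.00, 3.8% | 1.67 |
| | 20×10 | 1.21, 22.0% | 1.00, 5.0% | 1.64 |
| | 12×50 | 1.12, 21.3% | 1.01, 5.2% | 1.72 |
| ρ 1, ICC 0.2, SD 0.5 | 12×18 | 1.16, 18.2% | 1.00, 4.5% | 2.56 |
| | 20×10 | 1.23, 23.0% | 1.02, 4.3% | 2.33 |
| | 12×50 | 1.10, 19.3% | 1.00, 4.2% | 2.86 |

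**Hand check of the mixing** (12×18, ICC 0.2, SD 0.5, ρ 0.7). This uses the linear mixed-model weights, with residual variance about 1/0.20 = 5 on the logit scale.

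- Within-hospital dose variance given NIHSS: 0.8/1.16 = 0.690.
- Variance of facility means: 0.2 + 0.690/18 = 0.238.
- Between slope: (0.7 × 0.5/√0.2) × 0.2/0.238 = 0.657.
- Between weight: 0.238/(5 + 18 × 0.25) = 0.0251. Within weight: 0.690 × (17/18)/5 = 0.130.
- Between share: 0.0251/(0.0251 + 0.130) = 0.16.
- Single OR: exp(0.16 × 0.657) = 1.11, as simulated.

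The same steps give 1.14 for 20×10 and 1.06 for 12×50, also as simulated.

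**Adding unmeasured patient capacity** (log-odds ratio 0.5 per SD, ICC 0.2, SD 0.5). At ρ 0.7 the single term gives OR 1.30–1.36 with 39–69% rejection. Across ρ 0 and 0.7 the within term gives OR 1.22–1.26 with 17–48% rejection. The split therefore removes the facility part only.

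**The between term.** Where its true coefficient is zero (ρ 0), it rejects in 6–11% of datasets, so its Wald test is somewhat liberal.

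**The case against.** A facility random effect is a conventional choice, and centring within facilities is a detail that an analysis plan often settles. A reader might infer from sections 2.3 and 2.14 that the protocol itself contradicts the random-effect assumption. It does not. It says that practice varies, on shared guidelines and within one region. Varying dose is not the same as dose correlated with residual outcome, and nothing in the text says that higher-dose hospitals do better or worse. At ρ 0 the planned model behaves properly. The size depends wholly on assumed inputs, and the milder settings give only 6.7–8.8%. The covariate list is open, so institutional covariates could weaken the correlation. The stated aim is an association, and the Discussion concedes that causality cannot be established and that unstandardised practice may add variability.

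A reader might also infer that the within-hospital term should replace the planned estimate. The documents do not support that either. MQS reflects the mobility level reached, so the within term carries confounding by patient capacity, and the design deliberately captures differences between hospitals. Which component answers the study question is a debatable choice of estimand.

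All of that stands. It limits the point to showing the two components and does not remove it. The single term is what section 2.14 fixes, sections 2.11 and 2.13 give a plausible route from hospital practice to both dose and outcome, and the Discussion's concession speaks of variability, not of bias in the dose coefficient. Larger clusters shrink the bias in the odds ratio (1.11 at 18 per site, 1.06 at 50) but leave the rejection rate about the same (11.2% and 10.7%).

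**Conclusion.** The point holds as a conditional weakness of a stated choice. If facility dose and facility effect are correlated, the primary odds ratio is not the within-hospital association and the reader cannot tell. With ρ 0.7–1, dose ICC 0.1–0.4 and facility SD 0.3–0.5, the planned term rejects a null within-hospital association in 6.7–23.0% of datasets (OR 1.04–1.23 per SD), against 3.8–6.2% for the within term across all settings without capacity confounding. At ρ 0 the planned term rejects in 4.8–5.8%. The conclusion is the same for 12 or 20 facilities. Whether the correlation exists, and how strong it is, the documents do not say; the study's own data could indicate it. The planned model is not shown to be invalid, and neither component would be causal.

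**What to change.** Keep the planned primary model and pre-specify a companion to it:

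1. Replace the MQS term by facility-mean MQS and the patient's deviation from that mean, and keep the random intercept and the covariates.
2. Report both odds ratios and their difference, with intervals, next to the planned estimate.
3. Do the same for the MQS-by-severity interaction.
4. State in advance that, if the two components differ, the single odds ratio will not be interpreted as a patient-level dose association.
5. State that the within term remains open to confounding by patient capacity, and the between term to case mix and quality of care.
6. Reconcile the Discussion's claim that rehabilitation policy and institutional staffing are controlled with the covariates in section 2.14: name them in a model or withdraw the claim.

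The cost is one extra parameter in the main model, with matching terms in the interaction model, and no new data. With about twelve facilities the between-facility term will be imprecise and its Wald test somewhat liberal, so a non-significant difference between the components should not be taken as evidence that they agree. Enrolment is scheduled to begin in June 2026, so this can be fixed before outcomes exist.
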